## Abstract

**Background:**

Recovery of upper limb function in individuals after a stroke remains challenging. Modified constraint-induced movement therapy (m-CIMT) has strong evidence for increasing the use and recovery of sensorimotor function of the paretic upper limb. Recent studies have shown that priming with aerobic exercise prior to task-specific training potentiates upper limb recovery in individuals with stroke. This protocol describes a randomized clinical trial designed to determine whether priming with moderate-high intensity aerobic exercise prior to m-CIMT will improve the manual dexterity of the paretic upper limb in individuals with chronic hemiparesis.

**Methods:**

Sixty-two individuals with chronic hemiparesis will be randomized into two groups: Aerobic exercise + m-CIMT or Stretching + m-CIMT. m-CIMT includes 1) restraint of the nonparetic upper limb for 90% of waking hours, 2) intensive task-oriented training of the paretic upper limb for 3 h/day for 10 days and 3) behavior interventions for improving treatment adherence. Aerobic exercise will be conducted on a stationary bicycle at intervals of moderate to high intensity. Participants will be evaluated at baseline, 3, 30, and 90 days postintervention by the following instruments: Motor Activity Log, Nottingham Sensory Assessment, Wolf Motor Function Test, Box and Block Test, Nine-Hole Peg Test, Stroke Specific Quality of Life Scale and three-dimensional kinematics. The data will be tested for normality and homogeneity. Parametric data will be analyzed by two-way ANOVA with repeated measures and Bonferroni’s adjustment. For nonparametric data, the Friedman test followed by the Wilcoxon test with Bonferroni’s adjustment will be used to compare the ratings for each group. To compare the groups in each assessment, the Mann-Whitney test will be used.

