## Methods

This study is a randomized, single-blinded, intention-to-treat controlled clinical trial in which 78 participants of both genders in a chronic stage poststroke will be randomized into two groups of 39 participants. One group will receive AE combined with m-CIMT, and the other group will perform stretching exercises combined with m-CIMT. The eligibility criteria are presented in Table 1.

**Table 1 Tab1:** Eligibility criteria

Inclusion criteria	
• Stroke resulting in hemiparesis at least six months prior (chronic) • Do not a present lesion in the two hemispheres • Clinical diagnosis of ischemic or hemorrhagic stroke • ≥ 35 and ≤ 80 years old • Participants must present a minimum active movement of 45° of shoulder flexion or abduction, 20° of elbow extension, 10° of wrist extension, 10° of abduction or extension of the thumb, and 10° extension in at least two fingers (metacarpophalangeal and interphalangeal joints) and thumb • Participants must present the ability to pick up a towel using any grip [28] • Participants must present asymmetric of upper extremity, ≤ 2.5 in the Motor Activity Log (MAL) Quantity Scale [10] • Participants must have the ability to remain seated without trunk and arm support for 1 min [29]	
Exclusion criteria	
• Upper limb movement deficits attributable to no stroke pathology	
• Clear signs of dementia or cognitive disorder, indicated in the Mini- Mental State Examination (scores based in years of education, below 13 for illiterate individuals, 18 for individuals with 1 to 7 years of the primary school and 26 for individuals over eight years after primary school) [30, 31] • Individuals with lesion in cerebellar	
• The individuals are smokers, alcohol, or users of illicit drugs at the time of evaluation • Individuals with structural alterations in the cardiovascular and respiratory systems that will contraindicate the aerobic exercise • Individuals with uncorrected auditory and visual deficits • Individuals who present any electrocardiogram alteration or not the cardiorespiratory stress test • Individuals with historical diseases or osteomioarticular alterations • Individuals with body mass index > 28 • Individuals with uncontrolled diabetes mellitus or hypertension, comprehension aphasia, apraxia	

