### Sample size

The sample size was calculated with G*Power software using the independent t-test, 85% power, alpha 0.05, and 20% drop-out. Data from the Nine-Hole Peg test proposed by Yoon et al. (2014) [29] were considered for this calculation. Thus, a sample size of 78 individuals (39 per group) is required for this study (Fig. 1). However, after collecting the first five participants per group, the sample size will be recalculated for the same variable.

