### Randomization and blinding

The randomization method will be matched by age and gender at 1:1 per-muted block randomization generation by a web-based randomization tool (www.random.org). This sequence will be performed independently and remotely by a blinded investigator who will not have contact with other research procedures. Randomization will be concealed until group allocation.

Participants will not be identified by their real names and will not be aware of which study arm they allocated. Thus, the assessors will also be blind, as they will identify the patients by codes and will not have contact with other research procedures. The same standards will be applied to the staff responsible for following the m-CIMT procedures. Data analysis will be conducted by a researcher who is not involved in any stage of recruitment, screening, assessment, or intervention.

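### The abstract says 62 will be randomised and the Methods say 78; if 62 are randomised and the assumed 20% are lost, power falls below the stated 85%

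*Protocol article*

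**What the plan says.** The Methods paragraph of the abstract states: "Sixty-two individuals with chronic hemiparesis will be randomized into two groups". The opening of the main Methods section states: "78 participants of both genders in a chronic stage poststroke will be randomized into two groups of 39 participants".

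The Sample size section supports the second figure. It describes the calculation as follows: "The sample size was calculated with G*Power software using the independent t-test, 85% power, alpha 0.05, and 20% drop-out". It concludes: "Thus, a sample size of 78 individuals (39 per group) is required for this study". The effect size and standard deviation are not printed; the section refers to Nine-Hole Peg Test data from a cited study. It then makes the figure provisional: "after collecting the first five participants per group, the sample size will be recalculated for the same variable". No result of that recalculation is reported.

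**The concern.** Both sentences describe the number randomised into the same two groups, so the difference cannot be explained as enrolled versus analysed. Both are current text in the future tense. A reader cannot tell which figure the trial is recruiting to.

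The gap is 16 participants, about the size of the drop-out allowance. If recruitment stopped at 62, the trial would have no allowance for the 20% loss that its own calculation assumes, and the analysed sample would be smaller than that calculation requires.

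**Working it through.** **Inputs from the article.** Independent t-test, power 85%, alpha 0.05 and drop-out 20% (Sample size); 1:1 allocation (Randomization and blinding); 62 (abstract) and 78, or 39 per group (Methods, Sample size). Whether the test is one- or two-sided is not stated, and no effect size is given.

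**Step 1: the drop-out step.** Number to randomise = evaluable number / (1 − drop-out).

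- In total: 62 / 0.80 = 77.5, rounded up to 78.
- Per group: 31 / 0.80 = 38.75, rounded up to 39.
- In reverse: 78 × 0.80 = 62.4, about 62.

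The cruder multiplication 62 × 1.20 = 74.4 does not reach 78. So 62, 20% and 78 fit together exactly if 62 is the evaluable number. Only this link can be reproduced; the t-test step cannot, because its effect size is missing.

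**Step 2: what remains if 62 are randomised.** 62 × 0.80 = 49.6, about 50, or 25 per group.

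**Step 3: back-solve an effect size (assumption).** For n per group and standardised difference d, the two-sided t-test has 2n − 2 degrees of freedom and non-centrality d × √(n/2). Power is the probability that a noncentral t variable falls outside ± the 97.5% point of the central t. Setting power to 0.85 at n = 31 gives d = 0.774, with non-centrality 0.774 × √15.5 = 3.05.

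**Step 4: power at 25 per group.** Non-centrality becomes 0.774 × √12.5 = 2.74, and power is 76.4% (76.8% by the normal approximation).

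**Step 5: vary the assumptions.** Each row takes the stated evaluable number as giving 85% power and evaluates 25 per group.

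| Evaluable number per group assumed to give 85% | Sides | Back-solved d | Power at 25 per group |
|---|---|---|---|
| 31 | two | 0.774 | 76.4% |
| 31 | one | 0.689 | 77.5% |
| 32.5 (65 × 1.2 = 78) | two | 0.755 | 74.4% |
| 39 (78 is itself the evaluable number) | two | 0.687 | 66.3% |
| 39 | one | 0.613 | 68.8% |

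Because n is rounded up to a whole number, a small range of d leads to 31 per group. Over that range, power at 25 per group is 76% to 78% two-sided and 77.5% to 79% one-sided. The overall range is therefore about 66% to 79%, below 85% throughout.

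**Step 6: the case of no loss.** With 62 randomised and everyone evaluable (31 per group), power is 85% by construction under the first reading, and 75.9% two-sided if 39 per group is the evaluable target.

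**The case against.** The strongest reply is that 62 need not be a mistake. The Sample size section plans a recalculation after five participants per group, and 62 could be its result. That cannot be excluded. But the article describes the recalculation as still to come and reports no outcome, and the Methods and Sample size sections still give 78. If 62 is a re-estimate, those sections are out of date and the calculation behind 62 is missing. A correction is needed either way.

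It can also be said that this is only a slip in the abstract, since the body is consistent in two places. That bears on the cost of the correction, not on the need for it: the number to randomise is a core design figure.

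Four stronger readings are tempting, and the article does not support them:

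- **That 62 is certainly the post-drop-out number.** The arithmetic fits, but the article never says where 62 comes from.
- **That randomising 62 cannot give 85% power.** The shortfall depends on losing the assumed 20%. Without loss, 62 gives 85% if 31 per group is the evaluable target.
- **That power falls to about 43%.** That figure (42.7%) comes from applying the 0.005 threshold that Statistical analysis sets for its ten planned comparisons. At that threshold, 31 evaluable per group already gives only 55.5% with the same d, so the 62-versus-78 difference accounts for about 13 points (55.5 − 42.7 = 12.8). The rest is a mismatch between planning alpha and analysis threshold, which is a separate matter.
- **That the registered target is also inconsistent.** The article gives only the registration number and date, so nothing can be said about the target held there.

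**Conclusion.** The concern holds in this form: the article states two incompatible numbers to be randomised, 62 and 78, and does not reconcile them. Only 78 agrees with its own sample-size statement. Reading 62 as the evaluable number before inflation is probable but remains an inference.

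If 62 are randomised and 20% are lost, power drops from 85% to about 76%, a loss of about 9 points. This assumes a two-sided test at 0.05, an effect size back-solved from 31 evaluable per group, and that the stated inputs still apply. Because the article gives no effect size, the figure should be quoted with its range of roughly 66% to 79%. The direction is the same under every assumption tried; the exact size is not established.

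**What to change.** State one number to randomise in the abstract, Methods and Sample size sections. On the stated inputs this is 78 (39 per group). The abstract should then be corrected, and 62, if kept, labelled as the number expected to be evaluable (31 per group) after 20% drop-out.

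If 62 is the real or re-estimated target, change the Methods and Sample size sections to say so. Report the calculation behind it, its inputs (effect size, standard deviation, sidedness and drop-out) and the resulting power after 20% drop-out. That power is about 76% if the stated inputs still apply; if the recalculation used new inputs, it must be worked out from those.

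In the first case the cost is a text correction to the abstract, with no change to the design. In the second it is a revised sample-size paragraph and an explicit statement of the lower power, or of the new inputs that justify 62.

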**Discussion:**

This study will provide valuable information about the effect of motor priming for fine upper limb skill improvement in people with chronic poststroke hemiparesis, bringing new evidence about the association of two therapies commonly used in clinical practice.

**Trial registration:**

This trial was retrospectively registered (registration number RBR-83pwm3) on 07 May 2018.

## Background

Stroke is one of the main causes of death and the leading cause of disability in adults worldwide [1–4]. Most poststroke individuals experience a reduction in the function on the affected upper limb [5], related to deficits in force generation, muscular atrophy, joint incoordination, sensitivity disturbances, or spasticity [6]. The reduction in function results in impaired sensorimotor performance during activities of daily living, which may lead to frustration and reinforce compensatory behaviors, such as learned nonuse.

Based on neural plasticity mechanisms [7], Modified Constraint-Induced Movement Therapy (m-CIMT) [8, 9] emerged to provide poststroke individuals with greater functional use of the paretic upper limb [10], reverse learned nonuse [11], and improve motor function and manual dexterity [12]. m-CIMT has high levels of evidence (level A) for the recovery of upper-limb poststroke according to recent guidelines [13, 14]. However, it is not known whether other therapies could prime the effects of m-CIMT.

Recent studies have indicated an enhancement of motor learning (acquisition and retention of motor skills) [15–18], as well as cognitive function (memory, attention, and concentration) [19] in healthy adults when aerobic exercise (AE) was associated with training of specific abilities (motor or cognitive training). According to the literature, the sequence and intensity of AE impact the learning process [20] and might facilitate improvements in motor function or motor memory consolidation processes. The retention of motor tasks improves when performed 15 min after high-intensity interval AE compared to moderate and low-intensity exercise [21, 22]. Learning was greater when AE was achieved using a bicycle compared to a treadmill [23]. A recent study demonstrated that AE on a cycle ergometer, when associated with task-specific training, improves the sensorimotor function of the upper limb [24]. Currently, there is more evidence supporting AE as a method of priming lower limb motor recovery [24, 25]. However, to date, no studies have investigated the effect of AE on fine motor control or relearning of lost upper extremity movement using motion analysis and manual dexterity evaluation [21].

Considering a type of implicit learning, motor priming has been used in neurorehabilitation to facilitate motor learning [22, 26]. The priming theory presumes that when the brain is activated using an intervention delivered prior to the motor learning intervention, it will become more responsive to motor training due to increased neural activity. This “therapeutic window” may result from the modulation of long-term potentiation or long-term depression, such as mechanisms [22, 27, 28]. Movement-based priming, using repetitive or continuous, unilateral or bilateral movements, is an important method of priming the motor cortex in neurorehabilitation [22].

This protocol describes a single-blinded, randomized clinical trial designed to determine whether AE, as a form of movement-based priming, has an effect on the outcomes of m-CIMT, specifically the recovery of the skill of paretic upper limb in persons with chronic stroke. We hypothesize that AE will potentiate m-CIMT, resulting in improved manual dexterity in people in the chronic phase poststroke.

## Methods

This study is a randomized, single-blinded, intention-to-treat controlled clinical trial in which 78 participants of both genders in a chronic stage poststroke will be randomized into two groups of 39 participants. One group will receive AE combined with m-CIMT, and the other group will perform stretching exercises combined with m-CIMT. The eligibility criteria are presented in Table 1.

**Table 1 Tab1:** Eligibility criteria

Inclusion criteria	
• Stroke resulting in hemiparesis at least six months prior (chronic) • Do not a present lesion in the two hemispheres • Clinical diagnosis of ischemic or hemorrhagic stroke • ≥ 35 and ≤ 80 years old • Participants must present a minimum active movement of 45° of shoulder flexion or abduction, 20° of elbow extension, 10° of wrist extension, 10° of abduction or extension of the thumb, and 10° extension in at least two fingers (metacarpophalangeal and interphalangeal joints) and thumb • Participants must present the ability to pick up a towel using any grip [28] • Participants must present asymmetric of upper extremity, ≤ 2.5 in the Motor Activity Log (MAL) Quantity Scale [10] • Participants must have the ability to remain seated without trunk and arm support for 1 min [29]	
Exclusion criteria	
• Upper limb movement deficits attributable to no stroke pathology	
• Clear signs of dementia or cognitive disorder, indicated in the Mini- Mental State Examination (scores based in years of education, below 13 for illiterate individuals, 18 for individuals with 1 to 7 years of the primary school and 26 for individuals over eight years after primary school) [30, 31] • Individuals with lesion in cerebellar	
• The individuals are smokers, alcohol, or users of illicit drugs at the time of evaluation • Individuals with structural alterations in the cardiovascular and respiratory systems that will contraindicate the aerobic exercise • Individuals with uncorrected auditory and visual deficits • Individuals who present any electrocardiogram alteration or not the cardiorespiratory stress test • Individuals with historical diseases or osteomioarticular alterations • Individuals with body mass index > 28 • Individuals with uncontrolled diabetes mellitus or hypertension, comprehension aphasia, apraxia	

### Sample size

The sample size was calculated with G*Power software using the independent t-test, 85% power, alpha 0.05, and 20% drop-out. Data from the Nine-Hole Peg test proposed by Yoon et al. (2014) [29] were considered for this calculation. Thus, a sample size of 78 individuals (39 per group) is required for this study (Fig. 1). However, after collecting the first five participants per group, the sample size will be recalculated for the same variable.

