### Statistical analysis

Demographic characteristics, such as weight, height and body mass index, will be presented as the mean and standard deviation. Median, maximum and minimum values will be used to describe poststroke time and UE-FMA score.

For all dependent variables, normality (Kolmogorov-Smirnov) and homogeneity (Levene) tests will be applied. If the variables present a normal and homogeneous distribution, then two-way analysis of variance with repeated measurements and Bonferroni’s correction will be used to examine the effect of group-by-evaluation time interaction, group (AE + m-CIMT and Stretching + m-CIMT), and evaluation time (baseline, 3, 30 and 90 days after the intervention). To protect against Type I error, Bonferroni’s correction will be used. Thus, each of the 10 planned comparisons will have to achieve *p* = 0.005 for statistical significance. The partial eta squared (η^2^) will be used to determine the effect size of the intervention. The mean difference from pre- and post-interventions and the corresponding 95% confidence interval (95% CI) will be calculated for each group (EA + m-CIMT and Stretching + m-CIMT) in order to estimate the effect of the intervention.

Otherwise, the Friedman test (*p* < 0.05) will be used followed by the Wilcoxon test with Bonferroni’s adjustment (*p* < 0.008) to compare evaluation time for each group baseline, 3 days, 30 days, 90 days after the end of treatment. The Mann-Whitney test with Bonferroni’s adjustment (*p* < 0.012) will be used to compare the groups in each time evaluation (EA + m-CIMT and Stretching + m-CIMT).

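### The 85% power is computed at alpha 0.05, but the planned comparisons are judged at 0.005 or 0.012, where power for the sized single-visit contrast is about 55% or 67%

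*Protocol article*

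**What the plan says.** The Sample size section bases the trial on one two-group comparison of the Nine-Hole Peg Test: "The sample size was calculated with G*Power software using the independent t-test, 85% power, alpha 0.05, and 20% drop-out". It concludes that "a sample size of 78 individuals (39 per group) is required for this study". Data from a cited Nine-Hole Peg study "were considered for this calculation", but the assumed difference, the standard deviation and the number of tails are not given. The same section plans a recalculation on the same variable after five participants per group and mentions no change of alpha.

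The Statistical analysis section sets the decision thresholds. In the parametric route, a two-way repeated-measures ANOVA examines group, time and their interaction, and "each of the 10 planned comparisons will have to achieve *p* = 0.005 for statistical significance". In the rank route, Mann-Whitney tests at p < 0.012 "will be used to compare the groups in each time evaluation".

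**The concern.** A power figure belongs to a particular test at a particular significance level. The 85% was obtained at 0.05. The between-arm comparison it was computed for is later judged ten times more strictly in the parametric route (0.05/0.005 = 10) and about four times more strictly in the rank route (0.05/0.012 = 4.2). The document does not connect the two levels.

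Manual dexterity is the trial's stated hypothesis and the Nine-Hole Peg Test is the sizing variable. If a Nine-Hole Peg comparison between arms fails at 0.005, a reader relying on the stated 85% will treat that as stronger evidence against aerobic priming than it is. The planned recalculation would carry the mismatch forward if it again uses 0.05.

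**Working it through.** **Inputs.** From Sample size: independent t-test, alpha 0.05, power 85%, drop-out 20%, 39 per group. From Statistical analysis: thresholds 0.005 and 0.012. Assumed because not stated: two-sided testing (a one-sided variant is shown) and the standardised effect d (back-solved).

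**1. The plan's own figure.** The total cannot be rebuilt from first principles without an effect size, but the drop-out step reproduces: 31/(1 − 0.20) = 38.75, rounded up to 39 per group, 78 in total. So 31 evaluable per arm is the number behind the 85%. The Abstract's 62 equals 2 × 31.

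**2. Implied effect.** For n per arm, the t statistic has df = 2n − 2 and noncentrality d√(n/2). Power is the probability that it exceeds the critical value t(1 − α/2, df). With n = 31, df = 60 and critical value 2.000, setting power to 0.85 gives d = 0.774, so the noncentrality is 0.774 × √15.5 = 3.05.

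**3. Same contrast at the planned thresholds.** The effect and n stay the same and only the critical value changes: 2.591 at 0.012 and 2.915 at 0.005.

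| Case | 0.05 | 0.012 | 0.005 |
|---|---|---|---|
| 31 per arm, d = 0.774, two-sided | 85.0% | 67.5% | 55.5% |
| 39 per arm (no drop-out), d = 0.774 | 92.1% | 79.8% | 69.9% |
| 31 per arm, sized one-sided (d = 0.689), tested two-sided | 76.1% | 55.1% | 42.7% |

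For the Mann-Whitney test itself on normal data (relative efficiency 0.955), the 0.012 figure is about 65%.

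**4. Sensitivity to the unknown effect.** Back-solving d at 31, 32, 33 or 39 evaluable per arm gives 55.5% to 55.9% at 0.005 and 67.5% to 67.7% at 0.012. The loss comes from the change of alpha and hardly depends on the effect size.

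**5. What 85% would require.** With 31 per arm at 0.005, the detectable effect is d = 1.01 instead of 0.774. At d = 0.774, 85% power would need about 52 evaluable per arm at 0.005, or about 44 at 0.012.

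**6. Whether 0.005 covers the between-arm contrasts.** The 10 comparisons are not listed. Four visits give 6 pairs of visits and 4 between-group contrasts, 10 in all. The rank route's divisors fit that count: 0.05/6 = 0.0083 (printed as 0.008) and 0.05/4 = 0.0125 (printed as 0.012). This is an inference, but it is the natural reading.

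**The case against.** The strongest reply is that 55% is not the power of the plan. Three parts of it stand.

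- **The omnibus test.** The parametric route starts with the group-by-time interaction and the group effect, and no level is stated for either. A reader might infer that no between-group test is ever judged at 0.05. The document does not establish that.
- **Several visits.** A reader might also infer that the planned rule misses the assumed effect in nearly half of trials. That holds for one contrast at one visit. There are three post-treatment visits. In a simulation with 31 per arm and d = 0.774 sustained at all three, the chance that at least one contrast passes 0.005 is about 80% at a between-visit correlation of 0.5, falling to about 67% at 0.9. Both the sustained effect and the correlations are assumptions. The document gives neither.
- **Drop-out.** The lower figures assume the full 20% loss. With none, they rise to about 70% and 80%.

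Use of the baseline value could also help. A change-score t-test at 0.005 has power 55.5%, 69% and 84% at baseline correlations of 0.5, 0.6 and 0.7, if d = 0.774 refers to raw scores. But the sizing names an independent t-test and states no correlation, so this gain cannot be credited to the printed 85%.

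None of this removes the mismatch. The interaction test is not the test that was sized, and every single-visit variant of the sized contrast in the table falls short of 85% at the planned thresholds. The recalculation after five per group makes 78 provisional but does not change the alpha. Nor is this a detail that can be left to a separate analysis plan, since both levels are printed in this document.

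**Conclusion.** The point holds for the sized contrast. Power at one visit, at the effect implied by the plan's own figures, is about 55% at 0.005 and 67% at 0.012, not 85%. The range is about 43% and 55% (one-sided sizing, two-sided testing) to about 70% and 80% (no drop-out). It rests on a back-solved d, on normal data for the t-test figures, and on reading the 10 comparisons as including the between-arm contrasts. The drop-out arithmetic is correct. The defect is that the sizing and the decision rule use different alphas. Power for the interaction test, or for success at any of the three post-treatment visits, cannot be determined from the document.

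**What to change.** Make the sizing alpha and the decision alpha agree, in one of two ways.

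1. **Keep the thresholds and restate the power.** In Sample size, give about 55% power (67% in the rank route) for a single-visit contrast at the assumed effect, or say that 85% applies only to d of about 1.0 at 0.005.
2. **Name the sized test.** In Statistical analysis, state which Nine-Hole Peg between-arm test, at which visit, the 85% refers to, and that it is judged at two-sided 0.05. The Motor Activity Log and the Box and Block Test are also listed as primary outcomes, so say openly how they and the remaining comparisons are then handled.

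Under either option, state the assumed difference, the standard deviation and the number of tails, and use the same alpha in the recalculation after five participants per group.

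No added enrolment is needed. The first option costs a less favourable stated power. The second costs a lower status for the comparisons other than the sized one, including those on two listed primary outcomes unless they are provided for.
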